### Primary outcome

2.7.1

The primary outcome is the change in anxiety score from baseline to 3 days post-operation, measured using the HADS-A (25), with a score of ≥8 indicating clinically significant anxiety (26). The minimal clinically important difference (MCID) for the Hospital Anxiety and Depression Scale (HADS) is not fixed and varies across clinical contexts and analytical methods. Evidence from anchor-based studies and systematic reviews suggests that a change of approximately 1.5–2.0 points in the HADS total or subscale scores is generally considered clinically meaningful (27–29). Anxiety was assessed preoperatively in the ward on the day pre-operation (T0) prior to the first rTMS intervention, and the second intervention was administered in the pre-operative holding area on the day of operation. Postoperative anxiety scores were measured on days 1 (T1), 2 (T2), 3 (T3), and the 3rd month post-operation (T4).

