## Statistical analysis

2.11

All analyses will be conducted according to the intention-to-treat (ITT) principle, with participants assessed in their originally assigned groups regardless of protocol adherence or treatment received. Baseline demographic and clinical characteristics will be summarized to evaluate balance between the groups. Continuous variables will be assessed for normality using the Shapiro–Wilk test. Normally distributed variables will be presented as mean ± standard deviation (SD) and compared using independent t-tests, while non-normally distributed variables will be expressed as median (interquartile range, IQR) and analyzed using the Mann–Whitney U test. Categorical variables will be expressed as counts and percentages and compared using the chi-square test or Fisher’s exact test.

The primary outcome will be analyzed using a linear mixed-effects model, including treatment group, time, and treatment-by-time interaction as fixed effects, and a random intercept for each subject to account for within-subject correlations. Baseline HADS-A score, age, type of surgery, and relevant perioperative variables (e.g., anesthesia duration) will be included as covariates to control for potential confounding.

Secondary outcomes will be assessed via a linear mixed-effects model, comprising baseline values as covariates. Fixed effects will involve treatment, time, and the treatment-by-time interaction, with a random intercept for subjects accounting for within-subject variability. The treatment-by-time interaction will be initially examined. If significant, group differences and within-group changes at each time point will be assessed, with Bonferroni correction applied for multiple comparisons of baseline changes in anxiety scores. If not significant, only the major effect of treatment will be evaluated, and no Bonferroni correction will be utilized for time-specific treatment effects. Binary outcomes will be compared via the *χ*^2^ test or Fisher’s exact test, with relative risk (RR) and 95% confidence intervals (CI) reported.

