In the exploratory analyses, to investigate the heterogeneity of rTMS effects across subgroups within the anxious population, we performed a series of subgroup analyses for the primary outcome measure. The primary subgroup analysis was depending on the level of patient anxiety: individuals with a HADS-A score ≥8 were defined as having anxiety symptoms, with scores of 8–10 (mild), 11–14 (moderate), and 15–21 (severe). We also examined subgroup effects according to surgery type, PSQI score (≤15 vs. > 15), and FRAIL scale result (no frailty vs. pre-frailty or frailty). These analyses were conducted by adding an interaction term between the treatment group and the subgroup variable to the linear mixed-effects model for the primary outcome. Effect heterogeneity was examined by estimating the importance of interaction terms. The adjusted odds ratio (aOR) and its 95% CI for each subgroup were displayed in a forest plot.

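### Subgroup forest plot is to show adjusted odds ratios, but the stated linear mixed model of HADS-A change yields only mean differences in points

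*Protocol article*

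**What the plan says.** Section 2.7.1 of the protocol article defines a continuous endpoint at one landmark: "The primary outcome is the change in anxiety score from baseline to 3 days post-operation, measured using the HADS-A". HADS-A is also measured after surgery on days 1 and 2 and at month 3. The same section puts a clinically meaningful change at roughly 1.5–2.0 points.

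Section 2.11 gives the primary model: "The primary outcome will be analyzed using a linear mixed-effects model, including treatment group, time, and treatment-by-time interaction as fixed effects". It has a random intercept per patient, with baseline HADS-A among the covariates.

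For the exploratory part, section 2.11 says "we performed a series of subgroup analyses for the primary outcome measure". The method is "adding an interaction term between the treatment group and the subgroup variable to the linear mixed-effects model for the primary outcome". Heterogeneity is judged from that term: "Effect heterogeneity was examined by estimating the importance of interaction terms". The display is then fixed as follows: "The adjusted odds ratio (aOR) and its 95% CI for each subgroup were displayed in a forest plot".

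The subgroups are baseline anxiety severity, surgery type, PSQI and FRAIL.

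**The concern.** The outcome, the model and the effect measure do not fit together. The outcome is a score change and the model is linear, yet the reported quantity is an odds ratio. An analyst following section 2.11 would have to depart from it somewhere, and the article does not say where. The choice of a cut-off or of another model would then be open after the data are in.

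The forest plot would also be on a different scale from the primary result. A reader could not place a subgroup estimate beside the overall mean difference, or judge it against the 1.5–2.0 point range that the article itself offers.

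A second mismatch is smaller. The primary outcome is the change to day 3, and the primary model lets the treatment effect vary by visit. The added subgroup term does not involve time, so the heterogeneity test is not tied to day 3.

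**Working it through.** **Effect measure (no arithmetic needed).** The relevant statements side by side:

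- Outcome: HADS-A change, baseline to day 3, continuous (2.7.1).
- Subgroup model: the primary linear mixed model plus treatment-by-subgroup (2.11).
- Reported quantity: adjusted odds ratio with 95% CI (2.11).
- Dichotomised or ordinal form of the outcome for the subgroups: none given. A score of 8 or more is an entry criterion (2.2.1), a marker of clinically significant anxiety (2.7.1) and the lower bound of the severity strata (2.11). It is nowhere a response endpoint.
- Binary outcomes elsewhere in 2.11: "with relative risk (RR) and 95% confidence intervals (CI) reported", so the odds ratio does not match the plan's own convention either.

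In a linear model with identity link, each treatment coefficient is a difference in mean HADS-A points. No odds ratio follows from it.

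**Time and the subgroup term.** The plan states no figure for subgroup effects. The illustration borrows the pilot difference of 1.3 and SD of 2.9 from section 2.10. Those inputs give 2 × (2.9 × (1.960 + 0.842) / 1.3)² ≈ 78.1 per group (two-sided 0.05, power 0.80), in line with the stated 78; rounding up gives 79.

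Assumptions made here, not in the article: two equal subgroups, so 252 / 4 = 63 patients per treatment-by-subgroup cell; complete data; within-patient correlation 0.5; the effect difference between subgroups at visit t is d(t).

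With a random intercept and balanced data, a time-constant treatment-by-subgroup coefficient over K visits has expectation (1/K) × Σ d(t). This does not depend on the correlation.

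| Visits modelled | Where the 1.3-point difference lies | Two-way term | Three-way contrast at T3 |
|---|---|---|---|
| T1–T4 | T3 only | 1.3/4 = 0.33 | 1.30 |
| T1–T3 | T3 only | 1.3/3 = 0.43 | 1.30 |
| T0 and T3 | T3 only | 1.3/2 = 0.65 | 1.30 |
| T1–T4 | T1 only | 1.3/4 = 0.33 | 0 |
| T1–T4 | all four visits | 1.30 | 1.30 |

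Rows 1 and 4 show that the two-way term cannot tell day 3 from another day. Row 5 shows that it does recover the day-3 value when modification is constant.

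A simulation of row 1 with 126 per arm, 60 replicates and a true value of −1.3 gave a mean of −0.32 for the two-way term and −1.24 for the three-way contrast at T3.

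**Precision cost of the day-3 contrast.**

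- Standard error at one visit: 2.9 × √(4/63) = 0.731.
- Standard error of the two-way term: 0.731 × √((1 + (K − 1) × 0.5) / K), which is 0.578 for K = 4 and 0.597 for K = 3.

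**The case against.** The best defence is that the model is stated plainly, so the odds ratio is probably a wrong label. The analyses are called exploratory, and neither the primary test nor its sample size depends on them. This stands and limits the severity. It does not remove the contradiction, because the article names an effect measure and does not leave it to an analysis plan. Section 2.10 also cites the subgroup analyses as a reason for going beyond the dropout allowance (78 / 0.9 ≈ 87) to 126 per group.

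Several stronger readings are tempting, but the article does not support them:

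- *The two-way term does not test day 3 at all.* Too absolute: under constant modification it returns the day-3 value. The T3-only pattern above is an assumed extreme that nothing in the article suggests, and a time-constant term is a defensible exploratory choice.
- *The effect is averaged over T1–T4, including month 3.* The visits in the primary model are not stated, and section 2.7.2 lists anxiety scores at T1–T4 as a secondary outcome. Month 3 may not enter.
- *Analysts must either exponentiate a linear coefficient or dichotomise.* An ordinal model of the score would give an odds ratio without a cut-off. The article specifies none, so the mismatch remains. But exp(−1.3) = 0.27 illustrates a step nobody proposes, and the familiar efficiency of 2/π ≈ 64% concerns a median split, which appears nowhere in the plan.
- *The subgroups are underpowered.* No subgroup power figure is given or derived here, so this point does not rest on it.
- *The severity strata should be replaced by a continuous modifier.* That is a preference. Categorical strata with an interaction test are acceptable.

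**Conclusion.** The point holds. As written, section 2.11 asks for adjusted odds ratios from a linear mixed model of a continuous score change, and no endpoint or model that could supply them is specified for the subgroups. This follows from the text alone and needs no assumption.

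The secondary point holds in a limited form. The subgroup term tests modification averaged over the modelled visits, and it does not specifically test day 3 unless modification is constant over time. The dilution to between one half and one quarter rests on the T3-only pattern, balanced complete data and two to four visits in the model. It shows what could happen and does not forecast this trial.

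Severity is should-fix. A reader might infer that the main conclusion is at risk. It is not: the primary analysis is separate, and the subgroup analyses are labelled exploratory.

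**What to change.** In section 2.11, replace the adjusted odds ratio by the adjusted mean difference in HADS-A change from baseline to T3 (active minus sham) with its 95% CI, so that the forest plot shares the scale of the primary result. If an odds ratio is wanted as well, define its endpoint and model before unblinding.

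To match the primary outcome, take the subgroup effects and the heterogeneity test from a treatment-by-subgroup-by-time contrast at T3, with all lower-order terms in the model, or from an ANCOVA of the T3 score with treatment-by-subgroup. State which visits enter the model. If the time-constant term is kept on purpose, say that it describes modification averaged over those visits.

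The cost is the wording of two sentences, with no change to patients, data or procedures. The T3 contrast gives up some precision: under the assumptions above, its standard error is 0.731, against 0.578 for the two-way term with four visits.

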## Strategy for missing data

2.12

Throughout the clinical trial, any missing data will be carefully documented, with the reasons for and extent of missingness recorded. The pattern and mechanism of missing data will be evaluated to determine whether data are missing completely at random (MCAR), missing at random (MAR), or missing not at random (MNAR). If the loss to follow-up rate is below 10% during the follow-up period, the analysis will be based on complete-case data. If the loss to follow-up rate reaches 10% or higher, multiple imputation using chained equations (MICE) will be applied to account for potential bias under the MAR assumption.

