## Sample size

2.10

We conducted a pilot study comparing active versus sham rTMS in female patients. The pilot results showed a mean difference in anxiety scores of 1.3 between groups, with a standard deviation (SD) of 2.9. Depending on a significance level of 0.05 and a power of 0.80, we calculated a sample size of 78 patients/group via PASS 15.0. Accounting for a 10% dropout rate and pre-specified subgroup analyses, we aimed to recruit 126 participants/group to confirm sufficient study reliability.

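### The observed loss rate to month 3 decides between complete-case analysis and MICE, although the primary mixed model for day 3 can use all observed HADS-A data at any loss rate

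*Protocol article*

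**What the plan says.** Strategy for missing data (2.12) sets two branches. The first reads: "If the loss to follow-up rate is below 10% during the follow-up period, the analysis will be based on complete-case data". The second reads: "If the loss to follow-up rate reaches 10% or higher, multiple imputation using chained equations (MICE) will be applied", and the stated aim is to deal with bias under MAR. The section also says that the missingness will be evaluated to establish whether it is MCAR, MAR or MNAR. It does not define complete-case data.

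Statistical analysis (2.11) opens with "All analyses will be conducted according to the intention-to-treat (ITT) principle, with participants assessed in their originally assigned groups regardless of protocol adherence". For the primary outcome it says: "The primary outcome will be analyzed using a linear mixed-effects model, including treatment group, time, and treatment-by-time interaction as fixed effects". A random intercept per subject is added, with baseline HADS-A, age, type of surgery and perioperative variables as covariates.

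Primary outcome (2.7.1) says: "The primary outcome is the change in anxiety score from baseline to 3 days post-operation, measured using the HADS-A". HADS-A is measured at T0, on days 1 to 3 (T1 to T3) and at month 3 (T4); Table 1 agrees. Sample size (2.10) plans for loss with the words "Accounting for a 10% dropout rate".

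**The concern.** Four features of the rule work against the plan's own primary analysis.

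- **The trigger is a study result.** The method is not fixed until the loss has been counted, and the threshold sits exactly on the loss that the trial expects.
- **The trigger looks at the wrong window.** Follow-up runs to month 3, while the primary endpoint is reached on day 3. Patients who are lost after discharge can decide how day 3 is analysed.
- **The trigger ignores arm and reason.** Overall loss below 10% may be balanced, or may lie wholly in one arm. Withdrawal or dropout criteria (2.2.3) include not tolerating the stimulation and not completing follow-up visits. The first of these could plausibly differ between active and sham.
- **The low-loss branch gives up information that the model can use.** A likelihood-based mixed model handles incomplete records under MAR, provided that its mean and covariance structure are adequate. The plan invokes MAR only when loss is high and gives no reason for restricting the data when loss is low.

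At stake are which patients enter the primary analysis and, if loss is related to outcome differently by arm, the size and the error rate of the day-3 comparison.

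**Working it through.** **1. The plan's own sample size.** Inputs from Sample size (2.10): difference 1.3, SD 2.9, alpha 0.05 (taken as two-sided), power 0.80. n per group = 2 × [2.9 × (1.9600 + 0.8416) / 1.3]² = 78.12. The plan states 78; strict rounding up gives 79. The figure is reproduced for practical purposes. Inflation for 10% dropout gives 78 / 0.90 = 86.7, so 87; the plan attributes the rest of the 126 per group to subgroup analyses.

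**2. Where the switch falls.** 0.10 × 252 = 25.2. Hence 25 / 252 = 9.92% leads to complete cases and 26 / 252 = 10.32% leads to MICE. If each patient is lost independently with probability p, the chance of the complete-case branch is P(X ≤ 25), with X binomial(252, p):

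| True loss | P(complete-case branch) |
|---|---|
| 8% | 0.89 |
| 9% | 0.74 |
| 10% (planned) | 0.54 |
| 11% | 0.34 |
| 12% | 0.18 |

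At the planned loss the choice of method is close to a coin toss. If all 25 losses fell in one arm, that arm would lose 25 / 126 = 19.8% and the rule would still prescribe complete cases.

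**3. What complete case would discard.** Three readings are open.

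- *All visits T0 to T4 present* (the usual meaning with repeated measures): a patient with T3 observed and T4 missing is removed, and her observed primary endpoint with her.
- *T3 present*: T3 values are kept, but the T1 and T2 values of patients who miss T3 are discarded.
- *No imputation, all observed visits used*: nothing is discarded, and this branch is already the mixed model on available data.

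**4. Size of the possible bias on the all-visits reading.** This was simulated with 4,000 trials per scenario and 126 per arm. Assumptions: five visits with common correlation 0.5, SD 2.9 at each visit (so the SD of change is 2.9), and loss at month 3 only, with T3 always observed. The logit of loss changes by 1 per SD of the T3 score. Day 3 was compared by baseline-adjusted regression, a simple stand-in for the mixed model. A negative effect favours active stimulation. Mean loss was 6.7% to 9.4%.

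| Loss mechanism | True effect | All observed T3 | Complete cases |
|---|---|---|---|
| Same in both arms | 0 | 0.01; rejects 0.048 | 0.01; rejects 0.047 |
| Same in both arms | −1.3 | −1.29 | −1.24 |
| Active arm only, high scorers lost | 0 | 0.00; rejects 0.051 | −0.36; rejects 0.183 |
| Active arm only, high scorers lost | −1.3 | −1.30 | −1.56 |
| High scorers lost in active, low in sham | 0 | 0.01; rejects 0.049 | −0.34; rejects 0.181 |
| High scorers lost in active, low in sham | −1.3 | −1.29 | −1.59 |

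Among the simulated trials with loss below 10%, where the rule would actually apply complete cases, the two arm-dependent scenarios give almost the same type I error (0.180 and 0.179).

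**5. Power.** With difference 1.3 and SD 2.9, power is 0.945 at 126 per arm and about 0.92 after 25 losses, whether these are split evenly or all in one arm.

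**The case against.** The rule is prespecified and depends on overall loss, not on treatment results, and no inflation of error from the switch as such has been shown. That stands: the harm comes from the complete-case restriction, and the switch is unnecessary rather than dishonest.

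Several stronger readings are tempting, and the document does not support them.

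- *The rule discards observed day-3 data.* This follows only on the all-visits reading. The term is undefined, and on the no-imputation reading nothing is lost.
- *The rule flatly contradicts ITT.* Section 2.11 defines ITT by assigned group regardless of adherence, and complete-case analysis moves nobody between arms. The tension is about who is analysed. Even a likelihood analysis gains nothing on the outcome from a patient with no HADS-A after baseline.
- *Complete cases require MCAR.* They require less: the analysis stays valid if missingness depends only on covariates in a correctly specified model, such as arm and baseline HADS-A. Bias needs dependence on post-baseline scores or on unmodelled predictors of them.
- *Loss below 10% is the more likely branch.* At the planned loss its probability is 0.54, and the document gives no other loss rate.
- *The bias could reach 0.40 points.* If all 25 lost patients were in one arm and would have scored 2 points worse on day 3, the bias would be 25/126 × 2 = 0.40, or 31% of 1.3. The split and the 2-point gap are assumed. These patients have no day-3 value, so a likelihood analysis would remove that bias only in part. The figure does not measure what the fix gains.

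The absence of a detailed sensitivity analysis from an article is not itself a fault. The rule, however, is fixed in the article and is not left to an analysis plan.

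**Conclusion.** The point holds as a rule that should be changed; it does not invalidate the trial. The switch at 25 versus 26 patients, its match with the planned dropout and its blindness to arm and reason follow directly from the text. A complete-case restriction, on either of its two restrictive readings, drops partial records that the planned model can use.

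The size of the consequence depends on assumptions. If loss works the same way in both arms, the shift is about 0.05 points and type I error stays near 0.05. If month-3 loss depends on the day-3 score differently by arm, the assumed scenarios give a shift of about 0.26 to 0.36 points, which is 20% to 28% of the planned 1.3, and a type I error of about 0.18. Both results apply to the all-visits reading only. The direction comes from the assumed mechanism, and nothing in the document shows that such loss will occur. Power is not the issue.

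Separately, observed data cannot separate MAR from MNAR, so the promise to determine the mechanism cannot be kept. Neither branch uses its outcome, so this is a matter of wording.

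**What to change.** - Delete the 10% switch in Strategy for missing data (2.12).
- State that, whatever the loss rate, the mixed model of section 2.11 is fitted by direct likelihood under MAR to all randomised patients, using all observed HADS-A data. The day-3 contrast is the primary estimate. If the term complete case is kept anywhere, define it.
- Keep MICE as a prespecified sensitivity analysis that is run at any loss rate, preferably with a delta adjustment so that it also addresses MNAR.
- Replace the sentence on determining the mechanism with a commitment to describe missingness by arm, visit and reason.

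The cost is a change of wording in the protocol and analysis plan and one extra sensitivity analysis. The sample size does not change. The change should be made before unblinding.

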#### Withdrawal or dropout criteria

2.2.3

Participants may leave from the investigation at any time for any reason with no penalty. Continuous care will be ensured, and reasons for withdrawal will be documented. The investigator will discontinue the participation of any subject if any of the following conditions occur during the study:

Failure to strictly follow the study planFailure to complete follow-up visitsInability to tolerate repeated TMS interventionWithdrawal from the study due to personal reasons

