## Study interventions

2.5

All rTMS procedures were performed by professionally trained and experienced operators who had undergone standardized training prior to study initiation. The rTMS intervention is administered on the day before surgery and the day of surgery, resulting in two sessions per participant. This protocol is designed to accommodate the limited perioperative time window while providing a rapid, clinically feasible intervention.

Stimulation parameters are based on established neurophysiological principles. The right dorsolateral prefrontal cortex (DLPFC) is selected as the target region due to its role in negative emotional processing and its involvement in anxiety-related neural circuits. Low-frequency (1 Hz) stimulation is applied to reduce cortical excitability and modulate prefrontal–limbic pathways. The entire procedure strictly followed a unified protocol to ensure consistency in coil positioning, stimulation parameters, and patient interaction.

First, a circular coil was used to locate the stimulation target. The primary motor cortex (M1) was clinically identified as the area 2 cm anterior and 1–1.5 cm lateral to the intersection of the naso-occipital line and the temporoparietal line on the patient’s scalp (i.e., the Cz point). The resting motor threshold (RMT) for each patient was then determined as a reference for setting the stimulation intensity, expressed as a percentage of the rTMS device’s maximum output (24). The RMT was defined, using the visual observation technique, as the lowest stimulation intensity capable of eliciting a visible contraction in the target muscle in 5 out of 10 trials while the muscle was completely relaxed (24). Subsequently, a figure-8 coil was used to target the right DLPFC. The center of the coil was positioned parallel to the patient’s scalp, with its midpoint aligned directly over the stimulation site. The rTMS treatment was then delivered at an intensity of 80–120% of the RMT using a low frequency of 1 Hz (21). Both groups will undergo the intervention using identical devices and operational procedures. However, in the sham rTMS group, the device will not deliver pulsed magnetic fields to the brain but will only produce similar audible clicking sounds and scalp sensations/vibrations mimicking those emitted during active stimulation.

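### Patients removed for not tolerating rTMS may have no post-operative HADS-A, so both missing-data rules in section 2.12 estimate the effect as if all had tolerated it, not the ITT effect promised in 2.11

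*Protocol article*

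**What the plan says.** Five parts of the protocol article bear on this.

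- **Section 2.11 (Statistical analysis)** places every analysis under ITT, "with participants assessed in their originally assigned groups regardless of protocol adherence or treatment received".
- **Section 2.2.3 (Withdrawal or dropout criteria)** states: "The investigator will discontinue the participation of any subject if any of the following conditions occur during the study". The conditions listed include not tolerating the stimulation and not adhering to the plan. The wording ends participation in the study, not only the stimulation.
- **Section 2.5 (Study interventions)** fixes the timing: "The rTMS intervention is administered on the day before surgery and the day of surgery, resulting in two sessions per participant". The first post-operative HADS-A is on day 1 (T1).
- **Section 2.7.1 (Primary outcome)**: "The primary outcome is the change in anxiety score from baseline to 3 days post-operation".
- **Section 2.12 (Strategy for missing data)** sets two rules by the size of the loss. Below 10%, complete cases are analysed; at 10% or more, "multiple imputation using chained equations (MICE) will be applied to account for potential bias under the MAR assumption". It also says: "The pattern and mechanism of missing data will be evaluated to determine whether data are missing completely at random (MCAR", with MAR and MNAR as the other possible answers. No step in the section depends on which answer is reached.

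**The concern.** The patients who make an ITT effect differ from an effect in adherers are those who stop treatment or depart from the plan. Section 2.2.3 takes these patients out of the study, and at a point where they may have a T0 score and nothing later. Section 2.11 asks for their day-3 outcome; section 2.12 has to supply it or do without it.

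Complete-case analysis leaves them out. Imputation under MAR, with only T0 and covariates to work from, fills in day 3 from patients in the same arm who stayed. Either way the active arm is represented by those who tolerated rTMS. At stake is an estimate labelled ITT that answers a different question, with an error that favours rTMS if non-tolerators lose benefit.

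The statement about determining the mechanism adds a second difficulty: it suggests a check against MNAR that the data cannot provide and that the stated rule does not use.

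**Working it through.** **Inputs from the documents.** Section 2.10 gives a difference of 1.3 points, SD 2.9, significance level 0.05, power 0.80, 78 evaluable per group, 10% dropout and 126 recruited per group.

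**The plan's own figure.** n per group = 2 × [2.9 × (1.960 + 0.842) / 1.3]² = 78.1, or 79 rounded up. The t-test version gives 79.1, or 80. The stated 78 is reproduced to within 2 patients with a two-sided test, so 1.3 and 2.9 can be used as they stand.

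**Assumptions.** Neither of these is in the documents:

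- f = share of the active arm removed for intolerance with no post-operative score.
- r = share of the benefit that such a patient keeps. She may have had one session.

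I also take 1.3 as the effect in patients who complete rTMS, and non-tolerators as otherwise like completers with the same baseline.

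**Formula.**

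- Effect regardless of treatment received = 1.3 × (1 − f) + 1.3 × r × f = 1.3 × [1 − f(1 − r)].
- Target of complete cases, or of MAR imputation with arm in the model = 1.3.
- Overstatement = f(1 − r) × 1.3.

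| f | ITT effect, r = 0.5 | Overstatement | ITT effect, r = 0 | Overstatement |
|---|---|---|---|---|
| 2% | 1.29 | 0.01 | 1.27 | 0.03 |
| 10% | 1.24 | 0.07 | 1.17 | 0.13 |
| 20% | 1.17 | 0.13 | 1.04 | 0.26 |

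Loss in the sham arm does not enter the formula, because a sham patient who stops has no rTMS benefit to lose.

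**Check by simulation.** This used 126 per arm, residual SD 2.9, r = 0, an assumed baseline mean of 11 and SD of 2.5, baseline only for non-tolerators, regression-based multiple imputation with arm and baseline, 10 imputations and 1,500 replicates.

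| Intolerance, active / sham | True ITT effect | Imputation with arm | Complete case | Imputation without arm |
|---|---|---|---|---|
| 10% / 0% | 1.16 | 1.29 | 1.29 | 1.24 |
| 10% / 10% | 1.18 | 1.31 | 1.31 | 1.16 |
| 15% / 5% | 1.10 | 1.29 | 1.30 | 1.15 |
| 20% / 0% | 1.03 | 1.29 | 1.29 | 1.16 |

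With arm in the model, imputation and complete-case analysis agree and both return about 1.3. Omitting arm pulls the estimate towards zero, but it does not target the ITT effect either: it lies above it in three rows and slightly below in one.

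**Power.** With 126 per arm, power is 0.945 for an effect of 1.30, 0.893 for 1.17 and 0.812 for 1.04.

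**MAR versus MNAR.** The two differ in whether missingness depends on the unobserved day-3 score once the observed data are taken into account. The observed data contain no information on that. A test can speak against MCAR; it cannot choose between MAR and MNAR. The choice between the two rules in section 2.12 depends on the loss rate alone.

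**The case against.** **This belongs in an analysis plan that is not shown.** Multiple imputation under a declared MAR assumption is a standard main analysis, and MNAR sensitivity analyses are often placed in the SAP. That is fair, and their absence from the article is not the point. What stands is a conflict between rules the article does state: the removal rule in 2.2.3, the ITT promise in 2.11 and the two branches in 2.12.

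**Imputation is not the cause.** A reader might infer that MICE creates the bias and that the branch below 10% is safe. The simulation shows otherwise: complete-case analysis gives the same answer. The source is the removal of these patients before any post-operative score.

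**The 10% threshold is not an intolerance rate.** A reader might equate the two. Section 2.12 counts loss over follow-up, which runs to month 3, whereas the primary endpoint is day 3. A patient lost only at month 3 has her day-3 score and adds nothing to this bias. The 10% in section 2.10 is also an overall allowance, not specific to arm or reason. Nor does the article say whether removal for intolerance counts towards the threshold. This objection stands, and it is why the size can only be given as a range.

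**The upper figures are extreme.** A gap of 0.26 needs one active patient in five removed for intolerance with no benefit kept. Even then power for the ITT effect stays above 0.80. The sham is described as giving similar sounds and sensations, so much higher intolerance under active stimulation is not established. That bears on how large f is; the formula needs only f above zero and r below one.

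**False positives.** A reader might also infer an inflated type I error. The mechanism here does not support that: with no true effect there is no benefit to credit, and f(1 − r) × 0 = 0. Inflation would need a separate assumption that dropouts in the active arm do worse for other reasons, and the documents give no basis for one.

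**Conclusion.** The point holds as a mismatch between the stated question and the stated analysis. If patients removed under section 2.2.3 contribute no post-operative HADS-A, both branches of section 2.12 estimate the effect had everyone tolerated rTMS, while section 2.11 promises the effect regardless of treatment received.

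The size is not known, because the article gives no intolerance rate. It is negligible if intolerance is rare and reaches 20% of the planned effect (0.26 / 1.3) only at the top of the range shown. These figures assume that arm is in the imputation model and that non-tolerators differ from completers only in the benefit lost.

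The statement that the data will determine MAR or MNAR is wrong at any dropout rate, though correcting it alone would change no result. This is an improvement the sponsor should make. It does not show that the trial's conclusion would be unsafe.

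**What to change.** 1. **Sections 2.2.3 and 2.11.** Reconcile them by separating stopping rTMS from leaving the study. State that a patient who stops rTMS or departs from the plan remains in follow-up, with HADS-A collected to day 3 where she consents. This concerns data collection only; when stimulation stops is not at issue. It addresses the cause, since a day-3 score that is observed needs no imputation.
2. **Section 2.12, mechanism.** Replace the claim to determine the mechanism with a description of missing data by arm, reason and visit. Say whether removal for intolerance counts towards the 10%.
3. **Section 2.12, analysis.** Keep the MAR analysis, and state that arm is in the imputation model. Under either branch, pre-specify a sensitivity analysis for missing day-3 HADS-A: imputation from the sham arm (reference-based) for active-arm patients who stopped rTMS, and a delta-adjusted tipping-point analysis for other missing scores. Report both as sensitivity results, not as a condition for a positive claim. The sham-based version corresponds to r = 0, so it is cautious for a patient who keeps some benefit.

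The cost is a few sentences, a little programming and follow-up of patients who stop rTMS at visits already scheduled. No extra patients are needed. The downside is a sensitivity estimate somewhat less favourable to rTMS.
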